##### Musculoskeletal ultrasound examination

The Supersonic Aixplorer ultrasound diagnostic system, situated in the ultrasound department of our hospital, will be utilized for musculoskeletal examinations. This system employs equipped with a 15l linear array probe that operates within a frequency range of 4–15 MHz, making it particularly well-suited for detailed imaging in this area (35).

##### Positioning

To assess the trapezius muscle, the patient should lie in a prone position; with a soft, minimal-thickness U-shaped pillow placed under the forehead. This setup allows the patient's arms placed alongside the head to ensure neutral cervical alignment and full muscle relaxation. For the sternocleidomastoid assessment, patients will be positioned laterally, with a pillow at shoulder- height to maintain a neutral alignment of the head and neck, thereby facilitating full relaxation of the neck and shoulder areas.

##### Measurement location

The anatomical site for measuring the sternocleidomastoid muscle will be taken at the midpoint between the sternal notch and the mastoid process. In the case of the trapezius muscle, the measurement location will begin 2 cm lateral to the C4 spinous process for the trapezius (35).

##### E value measurement

The patient should maintain the prescribed position to ensure complete relaxation of the neck muscles. The examination begins with a standard two-dimensional ultrasound, which involves scanning the muscle tissue longitudinally and subsequently performing a transverse scan while keeping the probe aligned with the muscle fibers. Throughout this process, the ultrasound beam will be positioned orthogonal to the muscle fibers, enabling the visualization of muscle echoes and the arrangement of fibers. Emphasis is placed on achieving a clear view of the target muscle fibers. After this initial scanning, the elastography mode, specifically shear wave elastography (SWE), will be activated to cover the area of interest for the purpose of creating a tissue elasticity map. The system will automatically calculate the elasticity (E) value of the muscle tissue within this designated region of interest. Measurements will be taken three times, and the average values will be recorded.

##### Muscle thickness measurement

The patient will stay in a relaxed position, ensuring that the neck muscles are completely at ease. The examination will begin with a standard two-dimensional ultrasound, starting with a longitudinal scan of the muscle, which keeps the probe's longitudinal axis aligned with the muscle fibers. This will be followed by a transverse scan; during the examination, the ultrasound beam will be kept perpendicular to the muscle fibers, which will help in clearly observing the muscle echoes and the arrangement of the fibers, focusing on obtaining a clear image of the target muscle fibers. The ultrasound device's built-in software will be used to measure the muscle thickness at the defined transverse section. Measurements will be taken three times, and the average of these readings will be recorded.

#### Secondary outcomes

##### Visual analog scale (VAS) for pain

This assessment tool features a visual analog scale that is about 10 centimeters long, divided into 10 increments, with the endpoints labeled “0” and “10.” A score of “0” indicates no pain at all, while a score of “10” represents the highest level of pain imaginable. As the scores increase, they correspond to greater levels of pain intensity, thereby making this scale useful for assessing the severity of neck pain.

##### Neck disability index (NDI)

This commonly used tool evaluates cervical functional status by examining neck pain, related symptoms associated with neck pain, and the capacity to carry out daily activities. It consists of 10 items and has a maximum possible score of 50 points. Higher scores indicate greater functional impairment.

##### Clinical efficacy assessment

The assessment of clinical efficacy will be classified into four categories following the “Standards for Diagnosis and Efficacy of TCM Orthopedic Diseases” and “Standards for Diagnosis and Efficacy of TCM Diseases” that categorize outcomes into four classifications: ① Cure—complete resolution of neck pain, stiffness, and tilt with full cervical mobility; ② Significant Effect: This indicates a notable reduction or improvement in symptoms like neck tilt, neck pain, and muscle stiffness, paired with a considerable enhancement in cervical movement. ③ Effective-moderate symptom improvement and partial restoration of motion; ④ Ineffective: This classification is used when there is no improvement in symptoms, including neck tilt, neck pain, and muscle stiffness, or if there is even a deterioration, with no significant enhancement in cervical movement. The overall efficacy rate will be calculated as: Efficacy rate = (number of cures + number of significant effects + number of effective cases)/total number of participants × 100%.

##### Follow-up observation

Assessment after treatment at the two-week mark, and again during a follow-up observation up evaluations will occur two weeks and six months after completion of treatment to assess symptom recurrence or sustained improvement.

### Statistical methods

Sample size estimation is based on comparisons of two proportions in a fully randomized design following He Yan's work, “Statistics in Traditional Chinese Medicine.” In this framework, the variable p represents the combined rate, while p1 and p2 indicate the known rates for each group. The required sample size for each group is denoted as n. The literature establishes the maximum efficacy rate at 93.5% and the minimum efficacy rate at 73.6%. Assuming equal sample sizes for both groups, *p* can be calculated as the average of *p*1 and *p*2, formulated as *p* = (*p*1 + *p*2)/2, with *q* defined as 1 − *p*. The formula for determining the necessary sample size is *n* = 8*pq*/(*p*1 − *p*2)^2^. Based on this calculation, *n* is estimated to be 28. Considering a projected dropout rate of 15%, the minimum number of observations needed for each group is adjusted to 32 participants to account for dropout, which is derived by dividing 28 by (1–0.15). To further improve the accuracy of the trial data and the resulting statistical outcomes, the sample size will ultimately be increased to 35 participants per group to enhance the reliability of the statistical results.

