**Methods:**

This study utilized a randomized controlled trial design, where eligible patients diagnosed with AARS were, randomly assigned (1:1) to either a treatment group (gentle manipulative technique combined with continuous traction) or a control group (traction plus cervical collar immobilization). The treatment group received treatment twice daily, five days per week, for two weeks. The control group received the same traction protocol but wore a neck brace immediately after each traction treatment. The primary outcome measure was musculoskeletal ultrasound (MUSU) findings, while secondary outcomes include Visual Analogue Scale (VAS) pain scores and Neck Disability Index (NDI) scores. Both groups were assessed at baseline, post-treatment, two weeks, and six months after treatment.

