### Outcome measures

#### Primary outcome

The primary measures of interest included muscle thickness that encompasses both the anterior-posterior dimension (APD) and the lateral dimension (LD), along with the Young's modulus value (E value).

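### The required sample size is derived for the efficacy rate, a secondary outcome, so it does not size the comparison on the primary ultrasound measures

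*Protocol article*

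**What the plan says.** The abstract states: "The primary outcome measure was musculoskeletal ultrasound (MUSU) findings". The Primary outcome section makes this concrete: "The primary measures of interest included muscle thickness that encompasses both the anterior-posterior dimension (APD) and the lateral dimension (LD"), together with the Young's modulus (E) value. All of these are continuous. The Statistical analysis section compares normally distributed measurements between groups with independent-samples t-tests and takes P < 0.05 as significant.

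The sample-size paragraph, under Statistical methods, works on a different kind of endpoint: "Sample size estimation is based on comparisons of two proportions in a fully randomized design". Its inputs are two rates: "The literature establishes the maximum efficacy rate at 93.5% and the minimum efficacy rate at 73.6" (per cent). The formula is n = 8pq/(p1 − p2)², from which n "is estimated to be 28" per group. This becomes 32 for 15% dropout and then 35, the last step justified only as making the results more accurate and reliable.

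The one efficacy rate that the article defines is in Clinical efficacy assessment, which falls under the Secondary outcomes heading: "The overall efficacy rate will be calculated as: Efficacy rate = (number of cures + number of significant effects + number of effective cases)/total number of participants". It is not named as primary anywhere.

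**The concern.** A required sample size answers the question of how many patients are needed to detect a given difference in a given outcome. Here that outcome is not the primary one. A reader who sees 28 per group given as the requirement, and 35 enrolled, may conclude that the ultrasound comparison is adequately sized with some margin. The article gives no target difference, SD or power for any ultrasound measure, so that conclusion has no support. A non-significant primary result could then be read as absence of an effect when the trial may simply have been unable to detect one of moderate size.

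The meaning of the two rates is also unclear. The paragraph describes p1 and p2 as rates already known for the two groups, and then fills them with the maximum and minimum efficacy rates from the literature. It does not say whether these are the expected rates for this treatment and this comparator.

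**Working it through.** **1. The plan's own figure.** Inputs from Statistical methods: p1 = 0.935, p2 = 0.736.

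- p = (0.935 + 0.736)/2 = 0.8355 and q = 0.1645
- pq = 0.13744 and (p1 − p2)² = 0.199² = 0.039601
- n = 8 × 0.13744/0.039601 = 27.76, rounded up to 28

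The stated 28 is reproduced, so it comes wholly from the efficacy rate. For dropout, 28/0.85 = 32.94, which rounds up to 33, while the article states 32. This has no consequence because 35 are enrolled.

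**2. What 35 per arm can detect on a primary measure.** Inputs: 35 per arm (70 children, 1:1), 15% dropout (35 × 0.85 = 29.75, about 30 evaluable) and the planned independent-samples t-test. Assumptions: two-sided 5% (the article gives no sidedness), one measure at a time, and no adjustment for several primary measures. The article gives no SD, so results are in SD units.

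The normal approximation for the difference detectable at 80% power is (1.960 + 0.842) × √(2/n):

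- n = 35: 2.802 × 0.239 = 0.67 SD
- n = 30: 2.802 × 0.258 = 0.72 SD

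Solving the t-test exactly gives slightly larger values:

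| Evaluable per arm | Detectable at 80% power | Power at 0.5 SD |
|---|---|---|
| 35 | 0.68 SD | 54% |
| 30 | 0.74 SD | 48% |

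Conversely, the size needed per group for 80% power (normal approximation, before dropout) depends on a difference that the article does not give: 63 at 0.5 SD, 44 at 0.6 SD, 33 at 0.7 SD and 25 at 0.8 SD.

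**3. The calculation on its own endpoint.** The usual two-proportion formula is n = 2pq(z_α + z_β)²/(p1 − p2)². A constant of 8 means 2(z_α + z_β)² = 8, so z_α + z_β = 2. At two-sided 5%, z_α = 1.96, which leaves z_β = 0.04 and power of about 52%.

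Power for 93.5% versus 73.6% is Φ{[0.199 − 1.96√(2pq/n)]/√[(p1(1 − p1) + p2(1 − p2))/n]}, which is Φ{[0.199√n − 1.96 × 0.5243]/0.5051}:

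- n = 28: (1.0530 − 1.0276)/0.5051 = 0.05, power 52%
- n = 30: (1.0900 − 1.0276)/0.5051 = 0.12, power 55%
- n = 35: (1.1773 − 1.0276)/0.5051 = 0.30, power 62%

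The standard formula asks for 54 per group for 80% power at two-sided 5%. With a one-sided 5% test, power would be about 65% at 28 and 73% at 35.

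**The case against.** Four points can be made for the plan.

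First, the efficacy rate is not foreign to the trial. The Objective section speaks of effectiveness and safety and adds the ultrasound assessment afterwards. This stands in part. It would be tempting to say that the 70 children bear no relation to the trial's main question, but the article supports only the narrower statement that they have no stated relation to the declared primary outcome.

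Second, a reader might infer that a literature maximum set against a literature minimum is the most optimistic effect possible. The documents do not establish this. The same paragraph calls the two figures known rates for the groups, so maximum and minimum may simply label the better and the worse arm. Only the ambiguity can be held against it.

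Third, a reader might infer that the trial is underpowered on ultrasound. This is not shown either. With no SD or target difference, 35 per arm may be enough, and for a difference of about 0.7 SD it is.

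Fourth, a journal article condenses the full protocol. That does not help here, because the article gives the calculation in full, with endpoint type, rates, formula, dropout and final size. The fault lies in what it states, not in something left out.

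**Conclusion.** The point holds as a mismatch of endpoints. The required size is stated for a secondary binary rate, the primary outcome is continuous, and no target difference, SD or power connects the two. The size of the gap is best put as what the trial can detect: about 0.68 SD with 35 per arm, or about 0.74 SD with 30 evaluable, at 80% power for any one ultrasound measure. For 0.5 SD the power is near one half. The calculation is also weak for its own endpoint, at about 52% power for 28 per arm and 62% for 35.

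These figures assume a two-sided 5% test, the planned unadjusted t-test and the 15% dropout that the article projects. Harsher or kinder figures are possible but need further assumptions. Counting six primary measures (three measures on two muscles, a count the article does not state) and applying a Bonferroni correction would raise the detectable differences to about 0.85 and 0.93 SD. A baseline-adjusted analysis would lower them, but the article plans none and gives no correlation. The defect is a justification attached to the wrong outcome, and it should be corrected before results are read. It is not a demonstration that 70 is too few.

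**What to change.** Keep 70 children and rewrite the sample-size paragraph as follows:

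- Say plainly that the size was not derived for the primary ultrasound outcome.
- State that, with the planned independent-samples t-test at two-sided 5% and without adjustment for several primary measures, 35 per arm gives 80% power for about 0.68 SD in any one measure and about 30 evaluable per arm gives 80% power for about 0.74 SD. Add that power at 0.5 SD is about 54% and 48%.
- Label the efficacy-rate calculation as relating to a secondary outcome and give its actual power for 93.5% versus 73.6% (about 52%, 55% and 62% at 28, 30 and 35 per arm), or remove it as the basis for the required size. If it stays, say whether the two rates are the expected rates for these two arms and where they come from.
- Mark any multiplicity-adjusted or baseline-adjusted figure as an assumption.

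The cost is one rewritten paragraph and a less favourable statement of what the trial can detect. No extra patients are needed, and the planned test does not change.

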### Statistical analysis

All data will be analyzed using SPSS version 22.0 software. Categorical data will be summarized as frequencies or percentages and compared using Chi-square tests. Ordinal data will be analyzed using rank-sum tests. For measurement data that follow a normal distribution and demonstrate homogeneity of variance, results will be presented as mean ± standard deviation (x ± s). Independent samples t-tests will be used for between-group comparisons, paired-sample t-tests for within-group comparisons. Non-normally distributed data will be analyzed with nonparametric rank-sum tests. A *P*-value < 0.05 will be considered statistically significant.

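### The sample-size formula with constant 8 gives about 52% power at its own answer of 28 per group; 80% power needs about 54

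*Protocol article*

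**What the plan says.** The only justification for the trial's size is in the protocol article under Statistical methods. It compares two proportions: "The literature establishes the maximum efficacy rate at 93.5% and the minimum efficacy rate at 73.6" per cent. It takes p as the mean of the two rates and q as 1 − p ("Assuming equal sample sizes for both groups"), and continues: "The formula for determining the necessary sample size is *n* = 8*pq"/(p1−p2)². The result is given as follows: "Based on this calculation, *n* is estimated to be 28".

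For 15% dropout, "the minimum number of observations needed for each group is adjusted to 32 participants to account for dropout", by dividing 28 by 0.85. The figure is then raised to 35 per group, 70 in all, which is described as a gain in reliability.

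The sample-size paragraph states neither power nor sidedness. The significance threshold is under Statistical analysis: a P-"value < 0.05 will be considered statistically significant". The test for rates is in the same section: "Categorical data will be summarized as frequencies or percentages and compared using Chi-square tests".

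**The concern.** The formula is given as a per-group size for two independent groups. In that setting the multiplier of pq/(p1−p2)² is 2(zα+zβ)², which is 15.7 for 80% power at two-sided 5%. The protocol uses 8, about half of that. The text calls the result necessary and treats everything above it as margin.

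A reader would therefore conclude that 35 per group comfortably detects a 20-point difference in efficacy rate. If the true power is nearer 55 to 62%, a real difference of the size the plan assumes would be missed about 38 to 45% of the time. A non-significant result could then be taken as evidence of no benefit from a trial believed to be adequately sized.

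**Working it through.** **Inputs**

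- p1 = 0.935, p2 = 0.736, equal groups (Statistical methods). Hence p = 0.8355, q = 0.1645, pq = 0.13744, p1 − p2 = 0.199 and (p1 − p2)² = 0.039601.
- α = 0.05 (Statistical analysis). Sidedness is not stated. Two-sided is assumed because the chi-square test is named; one-sided is shown as a variant.
- Power is not stated. 80% is assumed as the usual minimum; 90% is also shown.
- Dropout 15%; 35 randomised per group.

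**The plan's own figure**

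8 × 0.13744 / 0.039601 = 27.76, rounded up to 28. This reproduces.

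**What the constant implies**

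Setting 2(zα+zβ)² = 8 gives zα+zβ = 2.00. With zα = 1.96, zβ = 0.04 and the power is Φ(0.04) = 51.6%.

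**Size needed, two-sided 5%**

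- 80% power, simple form: 2 × (1.96 + 0.8416)² × 0.13744 / 0.039601 = 54.5, so 55 per group.
- 80% power, pooled variance under the null and separate variances under the alternative: [1.96√(2pq) + 0.8416√(p1q1 + p2q2)]² / (p1−p2)². With √(2pq) = 0.5243 and √(p1q1 + p2q2) = 0.5051, this is (1.0276 + 0.4250)² / 0.039601 = 53.3, so 54 per group.
- 90% power: 71 per group by the second form, 73 by the simple form (72.9).
- 80% power at one-sided 5%: 42 per group by the second form.

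So 28 is 28/54 = 0.52 of the size for 80% two-sided power, 28/71 = 0.39 of that for 90%, and 28/42 = 0.67 of that for 80% one-sided.

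**Power at the plan's sizes**

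Normal approximation, two-sided: power = Φ{[0.199√n − 1.96 × 0.5243] / 0.5051}. The exact column enumerates the binomial outcomes for the uncorrected chi-square test.

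| n per group | Two-sided 5%, approx. | Two-sided 5%, exact chi-square | One-sided 5%, approx. |
|---|---|---|---|
| 28 (the stated requirement) | 52.0% | 54.9% | 64.7% |
| 30 (35 × 0.85 = 29.75) | 54.9% | 57.9% | 67.4% |
| 35 (no dropout) | 61.7% | 64.9% | 73.4% |

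With a continuity correction or Fisher's test, exact two-sided power is lower: 36% at 28, 41% at 30 and 51% at 35. No cell of the table reaches 80%.

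**Dropout step**

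28/0.85 = 32.94, which rounds up to 33. With 32 enrolled, 32 × 0.85 = 27.2 complete, fewer than the plan's own 28.

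**The case against.** The strongest case on the other side has five parts.

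- **The origin of the 8 is unknown.** The formula is credited to a textbook that is not at hand. The value (1.96 + 0.84)² = 7.85 is close to 8, which suggests that the usual 80% constant was used without the factor 2 for two groups. That is an inference. The power shortfall does not depend on it.
- **The protocol claims no power level.** This is true, and the description of 28 as about half the needed size holds only against 80% power at two-sided 5%. The 52% figure at 28 needs no power target, only two-sided 5% and the plan's rates. One-sided testing does not reach 80% either.
- **The trial enrols 35, not 28.** This stands, and 62% is better than 52%. But the plan's own dropout assumption brings the number back to about 30.
- **The efficacy rate is a secondary outcome.** The primary outcome is ultrasound muscle thickness and Young's modulus. The four efficacy categories might also be compared by the rank-sum test that the plan gives for ordinal data. Both points stand: these power figures say nothing about the primary comparison or about an ordinal analysis. The article nevertheless offers no other basis for 70 children, and the calculation it prints is for two rates.
- **An article may leave detail to the full protocol or analysis plan.** That would excuse an omission. Here a formula is printed, its result is called necessary, and enrolment is built on it.

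The figures for Fisher's test and the continuity correction concern tests the protocol does not name, so they serve only as a sensitivity check. The 32-for-33 slip has no effect on enrolment.

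**Conclusion.** The sample-size statement is wrong as written. The fault lies in the formula's constant; the sum that produces 28 is correct. At two-sided 5% and the plan's own rates, 28 per group has about 52% power (55% by exact chi-square), and the planned 35 has about 55 to 62% (58 to 65% exact), depending on dropout. Reaching 80% needs 54 to 55 completers per group. The assumptions are the rates of 93.5% and 73.6%, a chi-square comparison of two rates, and two-sided testing. Relaxing the last to one-sided raises the range over 28 to 35 per group only to 65 to 73%. Separately, 32 should read 33 by the plan's own division.

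**What to change.** Rewrite the Statistical methods paragraph as follows.

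1. Replace the formula with n = 2(zα+zβ)²pq/(p1−p2)² per group, and state two-sided α = 0.05 and the power beside it.
2. Remove the statement that 28 per group is the required number, and correct 32 to 33 if that step is kept.
3. State what the planned size delivers, for example: 35 per group, about 30 after 15% dropout, gives roughly 55 to 62% power at two-sided 5% to detect 93.5% against 73.6%.
4. Report the difference in efficacy rates with a 95% confidence interval. At the planning rates the expected half-width is 1.96 × √(0.2551/n), which is 0.167 at n = 35 and 0.181 at n = 30, or about 17 to 18 percentage points.

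The cost is one reworded paragraph and a less favourable power statement. Enrolment need not change if the efficacy rate remains secondary. If the sponsor wants 80% power on that rate, 54/0.85 = 63.5, so 64 per group and 128 in total would be needed instead of 70. The correction does not in itself supply a justification for the ultrasound primary outcome.

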### Statistical analysis

All data will be analyzed using SPSS version 22.0 software. Categorical data will be summarized as frequencies or percentages and compared using Chi-square tests. Ordinal data will be analyzed using rank-sum tests. For measurement data that follow a normal distribution and demonstrate homogeneity of variance, results will be presented as mean ± standard deviation (x ± s). Independent samples t-tests will be used for between-group comparisons, paired-sample t-tests for within-group comparisons. Non-normally distributed data will be analyzed with nonparametric rank-sum tests. A *P*-value < 0.05 will be considered statistically significant.

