### Inclusion criteria

Participants must meet the following inclusion criteria: (1) fulfillment of the diagnostic criteria for atlantoaxial rotatory subluxation (AARS); (2) age between 6 and 14 years, regardless of sex; (3) voluntary participation with informed consent provided by the child's guardian; and (4) first episode of the condition with no treatment received within the preceding two weeks. All participants must commit to completing the entire two-week treatment protocol and follow-up assessments.

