### Randomization and allocation concealment

This investigation strictly follows the framework of randomized controlled trials conducted at a single clinical research facility. A statistician, who is not involved in the study, will use SPSS 22.0 statistical software to generate a sequence of random numbers for the 70 recruited patients, dividing them into two groups: a treatment group that will receive gentle myofascial adjustment therapy and a control group that will undergo traction combined with cervical collar fixation, with each group consisting of 35 participants. The statistician will match the sequence of patient visits to the generated random numbers to finalize the group assignments. These assignments will then be securely stored in opaque envelopes to ensure allocation concealment. During the treatment phase, the physician will access these envelopes in the order of the child's visits to retrieve the group code. The physician will record both the patient code and the group number. Thereafter, after obtaining informed consent and completing the basic information form, the envelopes will be opened in strict numerical order, ensuring that patients receive examinations and treatments as detailed within the envelopes.

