## Conclusion

In summary, this study proposes to employ the method of gentle tendon adjustment under continuous traction as the treatment approach, targeting pediatric patients with AARS. A clinical randomized controlled trial methodology will be adopted to observe changes in visual analogue scale (VAS) pain scores, neck disability index (NDI) scores, and alterations in cervical muscle morphology and elasticity before and after treatment. By objectively quantifying clinical efficacy through musculoskeletal ultrasound during sustained traction with gentle tendon manipulation, this study will clarify the clinical value of this approach for treating pediatric AARS, facilitating its future implementation.

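### Planned t-tests do not adjust for the baseline values collected, leave open whether post-treatment values or changes are compared, and sit beside within-arm paired tests that do not test the treatment effect

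*Protocol article*

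**What the plan says.** For continuous outcomes, the Statistical analysis section of the protocol article gives one rule: "Independent samples t-tests will be used for between-group comparisons, paired-sample t-tests for within-group comparisons". The fallback is "Non-normally distributed data will be analyzed with nonparametric rank-sum tests", and a P value "< 0.05 will be considered statistically significant". No covariate or model is named. The section does not say whether the between-group test uses the post-treatment value or the change from baseline, and it does not describe the paired tests as descriptive.

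The surrounding design is as follows.

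- The primary outcomes are continuous: muscle thickness in two dimensions (APD and LD) and Young's modulus (E value). VAS and NDI are secondary (Outcome measures).
- A baseline is collected: "Both groups were assessed at baseline, post-treatment, two weeks, and six months after treatment" (Abstract, Methods).
- The children vary in age: "age between 6 and 14 years, regardless of sex" (Inclusion criteria).
- Allocation is by a simple description: the statistician "will use SPSS 22.0 statistical software to generate a sequence of random numbers for the 70 recruited patients" (Randomization and allocation concealment). No stratification is described.
- The aim is put in before-after terms: the trial will observe "alterations in cervical muscle morphology and elasticity before and after treatment" (Conclusion, with similar wording at the end of the Background).

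**The concern.** Three things follow from the stated rule.

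1. **Precision.** In a trial of 70 children, stable differences between children stay in the error term when post-treatment values are compared. When changes are compared, the baseline measurement adds noise of its own. A covariate that removes most of this is already collected and is not used.
2. **Chance imbalance.** If the arms happen to differ at baseline, neither form of t-test corrects the estimate properly, and the two forms are pushed in opposite directions. Because the analysed quantity is not fixed, the two could give different answers from the same data.
3. **Within-arm P values.** A paired test in one arm measures treatment effect mixed with natural recovery and regression to the mean. Both arms receive traction, so both may improve. With a paired test in each arm under the same 0.05 rule, a result that is significant in one arm and not in the other can be read as a difference between treatments.

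**Working it through.** **Inputs from the article.** 35 per arm, 1:1 allocation, 15% projected dropout and a 0.05 threshold (two-sided assumed, as sidedness is not stated). Completers: 35 × 0.85 = 29.75, taken as 30 per arm.

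**The plan's own figure.** The sample size formula is n = 8pq/(p1 − p2)². With p1 = 0.935 and p2 = 0.736, p = 0.8355 and q = 0.1645, so n = 8 × 0.8355 × 0.1645 / 0.199² = 27.76, rounded to 28 as stated. That calculation concerns the efficacy rate. It gives no SD, effect size or correlation for the continuous outcomes, so it cannot settle the present question.

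**Assumptions.** A true difference of 0.5 SD; correlation ρ between baseline and follow-up of 0.3, 0.5 or 0.7; equal SD at both times.

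**Variance of the treatment estimate, relative to a t-test on post-treatment values**

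- Post-treatment values: 1
- Change from baseline: 2(1 − ρ)
- ANCOVA: 1 − ρ²

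ANCOVA relative to change is (1 − ρ²)/[2(1 − ρ)] = (1 + ρ)/2, which is below 1 for every ρ below 1.

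**Power** from the noncentral t distribution, 30 per arm, with the standardised effect 0.5 divided by the square root of the relative variance:

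| ρ | Variance, change | Variance, ANCOVA | Power, post-treatment | Power, change | Power, ANCOVA |
|---|---|---|---|---|---|
| 0.3 | 1.40 | 0.91 | 48% | 36% | 51% |
| 0.5 | 1.00 | 0.75 | 48% | 48% | 59% |
| 0.7 | 0.60 | 0.51 | 48% | 69% | 76% |

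Against the better of the two t-tests, ANCOVA gains about 4, 12 and 7 percentage points at ρ = 0.3, 0.5 and 0.7. Against the worse of the two it gains about 15, 12 and 28 points. The degree of freedom spent on the covariate changes these figures by less than 0.1 point.

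**Chance baseline imbalance.** With 35 per arm, the SD of the baseline difference is √(2/35) = 0.239 SD units. A gap of at least 1.96 × 0.239 = 0.47 SD, in either direction, arises in 5% of trials. Given a gap of that size, the expected shift is:

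- post-treatment comparison: ρ × 0.47 = 0.14, 0.23 and 0.33 SD at ρ = 0.3, 0.5 and 0.7;
- change comparison: (1 − ρ) × 0.47 = 0.33, 0.23 and 0.14 SD, in the opposite direction.

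**Within-arm tests.** Suppose both arms truly change by the same amount and each paired test has power π. The probability that exactly one is significant is 2π(1 − π): 2 × 0.3 × 0.7 = 42%, 2 × 0.5 × 0.5 = 50%, and 2 × 0.8 × 0.2 = 32%. In all three cases there is no treatment difference.

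**The case against.** The best defence is that the planned between-group test is sound. Under randomisation an unadjusted t-test is unbiased and controls its type I error, and its standard error already allows for chance baseline differences. This stands. A reader might infer from the imbalance figures that the analysis is biased, but they describe error conditional on an uncommon imbalance. They are not a systematic fault, and they are another face of the lost precision, so they should not be added to it.

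A reader might also infer that the plan ignores baseline altogether and claim the full rise from 48% to 76% at ρ = 0.7. The article does not support that. Its before-after wording makes a t-test on change at least as natural a reading, and against that test the rise is from 69% to 76%. At ρ = 0.3 the gain over post-treatment values is small. The correlations are assumptions throughout.

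Other stronger readings also fail:

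- The article nowhere says that the outcomes vary with age. For muscle dimensions this is a fair inference from the age range; for E value, VAS and NDI nothing is offered. Baseline adjustment would absorb most of any stable age effect.
- The four-category clinical efficacy rating is itself a judgement of improvement and has no baseline, so the point does not reach it.
- The article does not say that efficacy will be concluded from significance in one arm. The hazard is that the paired tests are planned without a stated role. ANCOVA alone would not remove it.
- Handling of unequal variances and the choice of a paired rank test are details commonly left to an analysis plan, which is not shown here. They are not faults of this article.

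The defence that an unseen analysis plan may supply ANCOVA is weak, because the article states the tests themselves and a plan with a different primary analysis would depart from it.

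**Conclusion.** The point holds as one of efficiency and clarity; the planned test is not invalid. The article commits to unadjusted comparisons for outcomes with a collected baseline, leaves the analysed quantity open, and gives within-arm P values no defined role. ANCOVA is more precise than a t-test on change for any ρ below 1, and more precise than a t-test on post-treatment values whenever ρ differs from 0, apart from the one degree of freedom. So it need not be known in advance which t-test would have done better. Under the assumed 0.5 SD effect, 30 completers per arm and ρ of 0.3 to 0.7, the gain in power runs from about 4 to 28 percentage points, depending on ρ and on which t-test was meant. The direction is secure; the size is not, because the article gives no SD, effect size or correlation. The within-arm concern does not depend on ρ. The change is recommended because it costs almost nothing, but the trial's validity does not hang on it.

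**What to change.** In the Statistical analysis section:

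- For APD, LD, E value, VAS and NDI, make the between-group analysis an ANCOVA of the post-treatment value on group, with the same measure's baseline value as covariate. Age may be added but is optional. Report the adjusted difference with its 95% confidence interval.
- State that efficacy conclusions rest only on this between-group contrast.
- Report within-group change descriptively, with confidence intervals and without P values.

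The cost is a few sentences of analysis wording. The data are already collected, and no extra patients, visits or measurements are needed. The wording should be settled before unblinded data are seen, so that the model cannot be called a post hoc choice.
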